While organising and handling acute referrals to mental health care have been investigated in a scoping review [42], to our knowledge research on different triage variants in non-acute referrals to CMHCs is still scarce. One Norwegian study investigated the degree to which patient triage based on written referral information corresponded to triage based on consultation with the patient. In many situations, the need determined from a written referral was considered reliable, but in almost half of the referrals (46%), a possible under- or overestimation was seen, indicating a potential risk of incorrect use of resources as well as a risk to patient safety [43]. Another study found that a gateway team operating between primary and secondary mental health care services could reduce inappropriate referrals [44]. One study on health care for children, adolescents, and families suggested that assessment in a triage clinic reduced the frequency of non-attendance at the first appointment, increased the number of cases with shorter treatment courses, and improved interdisciplinary work [45]. One study among students in university health services in the USA concluded that telephone triage enabled rapid clinical intervention at a time when increased efficiency is required [46].

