### Interventions

Treatment as usual (TAU): Ordinary procedures for admission to an outpatient clinic are followed, in accordance with the Norwegian Directorate of Health’s national prioritisation guide [15]. Referrals are assessed based on severity, and patients are placed on a regular waiting list (usually a waiting period of 1–4 months). They receive their first personal assessment from a therapist in a general outpatient clinic, who decides on further follow-up in accordance with the procedures in the outpatient clinic. There is no standard protocol for what TAU treatment would include, apart from it following national and international standards; each individual therapist is expected to choose the appropriate approach.

In TAU, the patient has been waiting for weeks to months before the first appointment. The patient is met by one therapist—experienced or inexperienced—who may be a psychiatrist, a medical doctor, a psychologist, a psychiatric nurse, or occasionally other health care personnel, such as social workers, physiotherapists, or occupational therapists, most with special training in mental health care. The traditional focus is on building a relationship and exploring the patient’s history to establish a diagnosis and then plan therapy. The first meeting in a standard outpatient clinic is in most cases followed by several assessment and treatment appointments. Therapists vary in how often they collaborate with other professionals. Interaction with other services occurs either sequentially or in parallel, with the patient often being the sole communicator among various stakeholders.

The medical record review performed 12 months after study inclusion registers the different collaboration partners as well as the amount and frequency of health services used.

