2)Early assessment team (EaT): The patient is scheduled for their first appointment in the CMHC with the EaT within 2–3 weeks after referral. In the first meeting, the patient meets with two therapists; in most cases, at least one of the therapists is experienced (a psychiatrist or a psychologist specialising in clinical adult psychology), and the other therapist is likely to be a psychiatric nurse or another psychiatrist or a psychologist. A clinical interview is conducted comprising the same topics as in a standard first appointment. Standardised psychometric questionnaires are not usually used in this first meeting: what is most important is the dialogue in which all aspects of life are discussed. Mental symptoms and current ailments are seen from medical, psychological, and contextual perspectives, including the vulnerabilities and strengths reported by patient as well as any sustaining factors from the past and present. Instead of focusing solely on psychiatric diagnosis, the evaluation entails an overall assessment which considers the severity of symptoms and functional impairment experienced by the patient, with a focus on life skills and possibilities.

Different solutions and possibly brief interventions are planned in collaboration with the patient and—if relevant—also with their informal network (i.e. relatives or next of kin) or professional collaborators (i.e. community health care, welfare services, GPs, or others). The team decides whether further assessment or treatment should be provided in the outpatient clinic, or whether any other follow-ups or interventions may be more appropriate; sometimes, a combination of these is applied. The team is flexible in terms of intensity and duration of intervention. Immediate short-term follow-up is possible with the EaT. If the patient’s mental health indicates a need for further standard specialised treatment (TAU after EaT), the patient is transferred to a therapist in the general outpatient clinic. If other means than TAU are expected to sufficiently relieve the patient’s suffering, their contact with the CMHC is ended. When the medical record review is performed 12 months after inclusion, different collaboration partners are registered, along with the amount and frequency of health services used.

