### Data collection

Data are collected through self-reported questionnaires using an electronic survey system by Checkware® [51]. After giving consent, the participants receive a link to the questionnaires, which are then open for answering for 14 days. Participants may be reminded up to two times per assessment point. The primary assessment points are at enrolment (T0), after the first meeting (T1), and then at 2 (T2), 4 (T3), 8 (T4), 12 (T5), and 24 (T6) months after inclusion, as well as after the last session (T7). If the treatment is not completed at 12 months, the questionnaires from T7 are sent after 12 months. Since waiting times before the first appointment differ in the two conditions, collection points at both 2 and 4 months post-inclusion were added.

Qualified healthcare personnel review the participants’ medical records. In addition, register data related to social security use, income compensation benefits, and sick leave will be collected from the Norwegian Labour and Welfare Administration (NAV). Demographic data are collected as part of the baseline questionnaire package (T0). See Table 1 for an overview of the data collection.

**Table 1 Tab1:** Schedule of enrolment, interventions, and assessment

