The *Working Alliance Inventory Short form Revised* (WAI-SR; [71, 72]) is a self-report questionnaire measuring the therapeutic alliance in three domains: agreement with the therapist on the goals of treatment, tasks required to achieve treatment goals, and the quality of the bond established between the patient and the therapist. The 12 items are rated on a 7-point scale ranging from ‘never’ to ‘always’. Higher scores indicate a stronger therapeutic working alliance, and total scores above 36 represent a positive alliance. The WAI-SR has demonstrated adequate psychometric properties [73]. The questionnaire will be administred to the participants at T1, which contains no other secondary measures for patients than the SRS (see below).

*The Session Rating Scale* (SRS; [74]) is used to elicit further information about how the patient experiences their first meeting with the therapist. The four-item self-report measure maps the goals and topics of the conversation, the relationship with the therapist, the therapist’s approach, and a general perception of the meeting. The structure of the SRS is based on a brief visual analogue scale (VAS), where the patient indicates a score on a continuous ten-point scale. The SRS was designed for use by clinicians to assess the therapeutic alliance during treatment, so that the therapist can change their approach or style if the client reports a negative experience. The SRS has solid reliability, sufficient validity, and high feasibility [74]. In this study, the questionnaire is administred to the participants at T1.

Self-reported demographic data at baseline (T0) also includes information about perceived history of cognitive function. Some questions from the *Rapid Assessment of Potential Intellectual Disability* (RAPID; [75]) are used, namely functioning at school, and whether the person has had learning difficulties or received adapted teaching at school. In the demographic data, we also ask if there are problems in different areas of life (e.g. housing, work and education, family relationships, accidents, etc.) and the extent to which the patient and therapist believe this affects the patient’s present functioning and symptoms. The form is based on findings from a Norwegian multicentre study of CRTs [76] and was also used in the pilot study evaluating the first 2 years of the EaT being operational [5].

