### Statistical analyses

The primary analysis of the outcomes will involve the 12-month time point (change in outcome from baseline to 12-month follow-up). A *t*-test will be performed to compare the randomised groups in terms of the primary outcome (WSAS) as well as the secondary outcomes; this test will be conducted within the framework of linear mixed models (LMM) based on data from all time points. Changes over time will also be estimated from the LMMs. If the assumptions for using LMMs are not met, the analyses can be carried out as separate comparisons at the 12-month follow-up. Due to the large sample, independent-sample *t*-tests can be considered according to the central limit theorem. Non-parametric tests will be used if they are considered more appropriate after the distribution of the data is inspected. The assumption of normal distribution for the residuals of the LMMs will be assessed using visual inspection of histograms and normal QQ plots. Due to the method for parameter estimation (maximum likelihood), the LMMs allow for missing outcome data at one or more occasions as long as data are missing at random (MAR); thus, data from all individuals will be included in the primary analyses.

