The sample size is quite large considering that this is a naturalistic clinical trial, and it has been calculated from power considerations for the primary outcome (WSAS). As of 20 September 2023, inclusion of participants had reached 50%; therefore, the research team is analysing baseline data from the self-reports for first half of the participants (*n* = 294), medical record data for the participant before randomisation, and data from therapists at T1 concerning their descriptive assessment of the life areas which are seen as part of the participant’s current situation and data. The goal is to describe the features of the sample as a whole. Depending on the amount of time left before inclusion is complete, the research group may study self-reported data from participants at T1 (WAI-S and SRS) and compare these variables between the groups; if this happens, corresponding analyses will be performed on the entire dataset when available and presented in a later article. No data related to primary or secondary outcomes at T2–T6 will be analysed before inclusion is complete. Baseline characteristics of the randomised groups will also be presented for the full sample after inclusion is complete. *P*-values < 0.05 will be considered statistically significant. No formal adjustments of multiple testing will be performed, due to multiple secondary endpoints, but the issue will be kept in mind when interpreting the results.

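### WAI and SRS exist only after a first meeting, so comparing them between the groups conditions on a post-randomisation event that the allocated arm may affect

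*Protocol article*

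**What the plan says.** The protocol article places WAI and SRS under Secondary outcome measures. Table 1 schedules both at the first meeting only. On the WAI, the Self-reported data section says "The questionnaire will be administred to the participants at T1, which contains no other secondary measures for patients than the SRS". Neither measure has a baseline or a later value.

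The route to T1 differs by arm. In the Interventions section, for EaT: "The patient is scheduled for their first appointment in the CMHC with the EaT within 2–3 weeks after referral". For TAU: "patients are placed on a regular waiting list (usually a waiting period of 1–4 months". The Randomisation and blinding section has patients randomised once they have consented, which is before any clinical meeting.

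In Statistical analyses, the randomised groups are compared on the primary and secondary outcomes by a t-test within a linear mixed model that uses all time points, the target being change from baseline to 12 months. The fallback is a separate comparison at 12 months. For the T1 measures, the group "may study self-reported data from participants at T1 (WAI-S and SRS) and compare these variables between the groups" before inclusion is complete. If it does, "corresponding analyses will be performed on the entire dataset when available and presented in a later article".

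**The concern.** T1 is triggered by an event and is not a fixed time from randomisation. A participant who improves, gives up, goes elsewhere or does not turn up before the first appointment never produces a WAI or SRS. For that person the value is undefined; it is not a missing observation that a model could recover. The length of the wait is part of what is randomised, so the arm may affect who reaches T1. If it does, and if reaching T1 is related to the score, the attenders being compared differ for reasons other than the quality of the meeting.

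The authors saw that the waits differ: the Data collection section says that the 2- and 4-month points were added for that reason. WAI and SRS are not collected at those points.

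What is at stake is the reading of two process measures. A difference in alliance or session rating among attenders could be published as an effect of EaT when part of it reflects who was still there to be asked.

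**Working it through.** **The plan's own figures.** No figure is given for WAI or SRS. The WSAS sample size reproduces: a two-sided t-test at 0.05 with 80% power, difference 3 and SD 10 needs 175.4, so 176 per group; 176/0.6 = 293.3, so 294 per group and 588 in total. It is used below only for the number randomised per arm.

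**Does the stated method apply?**
- Change from baseline to 12 months needs a T0 and a 12-month value. WAI and SRS have neither.
- A mixed model over all time points needs repeated values. Each measure has one.
- The fallback comparison at 12 months needs a 12-month value. There is none.

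What remains is a plain comparison of those who have a T1 score.

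**How large could selection be?** Attendance rates are not in the document. The following assumes 95% in EaT and 90%, 85% or 80% in TAU, and no true effect.

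*Worst case (trimming bound).* Let q = (pE − pT)/pE be the share of EaT attenders who would not have attended under TAU. If nobody attends only under TAU, and that share lies wholly in one tail of a normal score, the bias is at most φ(z_q)/(1 − q) in either direction.

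*Moderate selection.* Let the tendency to attend correlate ρ with the score, equally in both arms. The mean among attenders is ρ·φ(z_{1−p})/p, and the bias is the difference between the arms. For p = 0.95, 0.90, 0.85 and 0.80, φ(z_{1−p})/p is about 0.109, 0.195, 0.274 and 0.350. At 95% v 80% with ρ = 0.5, the bias is 0.5 × (0.350 − 0.109) = 0.12 SD. Type I error takes 294 randomised per arm, all attenders responding, and SE = √(1/nE + 1/nT).

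| Attendance EaT v TAU | q | Worst case (SD) | Moderate, ρ = 0.2 to 0.5 (SD) | Type I error, ρ = 0.2 to 0.5 |
|---|---|---|---|---|
| 95% v 90% | 0.053 | 0.11 | 0.02 to 0.04 | 5.5% to 8.0% |
| 95% v 85% | 0.105 | 0.20 | 0.03 to 0.08 | 6.7% to 15.8% |
| 95% v 80% | 0.158 | 0.29 | 0.05 to 0.12 | 8.5% to 27.6% |

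With ρ = 0 the bias is zero at any attendance rates. With equal attendance and the same selection in both arms it is also zero.

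**The optional early comparison.** From 25 October 2021 to 20 September 2023 is 695 days, or 22.8 months. 294/22.8 is about 12.9 participants a month, or 6.4 per arm. With steady accrual, an immediate data cut and the stated waits counted from randomisation, those still waiting would be:
- EaT, 2–3 weeks (0.46 to 0.69 months): about 3 to 4 of 147, or 2–3%.
- TAU, 1–4 months: about 6 to 26 of 147, or 4–18%.

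The EaT wait is stated from referral, so counting it from randomisation overstates the EaT figure. Unequal completeness would therefore arise from the calendar alone, even if everyone eventually attended.

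**The case against.** **The sentence is optional and modest.** It says only that the group may look at these scores, and it does not call the result an effect of EaT. An alliance cannot be rated without a meeting, so every such measure has this property. Covariates and sensitivity bounds are usually left to an analysis plan. Much of this stands and keeps the severity low. It does not remove the point: the article itself fixes a comparison between the groups, and the method it states for secondary outcomes cannot be applied to these two.

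**Stronger readings that the documents do not support.**
- *That the attenders are differently selected as a matter of fact.* A reader might infer this from the waits and from the Background, where one study suggested that "assessment in a triage clinic reduced the frequency of non-attendance at the first appointment". That study concerned children, adolescents and families, whereas this trial enrols adults. It makes a difference in attendance plausible and no more.
- *That the bias could be as large as the effect the trial is built to find.* The 0.29 SD figure is a worst case on assumed rates. The target of 3/10 = 0.3 SD is for WSAS at 12 months, so it is no benchmark for WAI or SRS.
- *That the plan never compares whether patients were seen.* Use of health services is a named outcome in the Abstract, and the 12-month record review registers its amount and frequency in both arms. It is fair to say only that first-meeting attendance is not separately named.
- *That the plan claims missing-at-random protection for T1 measures.* The statement "thus, data from all individuals will be included in the primary analyses" concerns the primary analyses with repeated outcomes. It makes no claim about WAI or SRS.

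**Conclusion.** The concern holds in limited form. WAI and SRS are post-meeting measures, so their comparison between groups is conditional on attendance, and the stated mixed model cannot handle them. That follows from the schedule and needs no assumption. Whether bias results, in which direction and how much, cannot be determined from the document. On assumed attendance of 95% v 90% to 80%, the range runs from zero (attendance unrelated to the score), through about 0.02–0.12 SD (moderate selection), to 0.11–0.29 SD (worst case, monotone attendance). None of these figures allows for attenders who do not return the T1 questionnaire. WSAS and the other self-reports collected at fixed times from inclusion are not affected. Severity is minor to moderate.

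**What to change.** 1. From the 12-month record review already planned, report and compare by arm the proportion of all randomised participants who attended a first meeting, and name it within use of health services. Report T1 questionnaire response by arm, also out of all randomised.
2. Analyse WAI and SRS as comparisons among attenders who responded, adjusted for T0 WSAS and CORE-OM. Add a sensitivity bound covering non-attendance and T1 non-response together. In the trimming formula this means replacing each attendance rate with the proportion of all randomised who supplied a T1 score, with the monotone assumption stated for both steps. Do not describe the results as effects of randomisation.
3. If the early T1 comparison is done, limit it to participants randomised long enough ago for the TAU wait to have elapsed.

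The cost is a paragraph of analysis text, one variable from records already being reviewed, and a smaller sample for any early comparison. The real downside is a weaker claim for WAI and SRS. The covariate adjustment helps only so far as baseline function and distress explain who attends and responds, which is why the bound is still needed.

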### Qualitative methods

In this study, we aim to investigate patients’ experiences with and the various aspects of a service innovation project in mental health care. The qualitative knowledge will complement the findings from the efficacy study and be important in the further development of the programme and any implementation studies. This part of the study will have an exploratory, qualitative design rooted in a phenomenological hermeneutic approach. Phenomenology aims to understand what the world looks like to participants and how they perceive and experience the world [81]. Such a design is particularly suitable for investigating the issues at hand, since experiences with admission interviews and assessments in elective mental health care for adults have so far been little studied. The data will further be analysed using reflexive thematic methodology [82]. In the analyses, we will build on the six steps proposed by Braun and Clarke [82], wherein researchers first familiarise themselves with the data (step 1) by either conducting or listening to interviews or reading transcripts, followed by coding (step 2), theme generation (step 3), and reassessment (step 4), which in turn is followed by defining and naming themes (step 5) and writing up the findings (step 6). In the process, we will strive to use Braun and Clarke’s newer reflexive approach to the method, central to which is taking into account the role of researchers in understanding and analysing data and in developing codes and topics [83].

### Data management

Methods for collecting and storing data have been developed in accordance with the regulations for clinical research at St. Olav’s Hospital. The Data Protection Official at the hospital has been consulted, and a secure area, provided by the hospital’s data department, has been created for data storage. The project and data are owned by St. Olav’s Hospital, Nidelv CMHC. To ensure anonymity, participants are given a non-identifiable study ID at the point of randomisation. The digital service for the self-reports has security level 4.

### Data monitoring and safety

No harmful consequences of participation in this study are anticipated; therefore, no stopping guidelines have been developed, and no interim analyses have been planned. Since participation in the study will not affect the patient’s right to health care and since no invasive procedures are performed, we do not consider that participation entails risk or inconvenience exceeding those possibly existing in standard mental health care. Furthermore, the intervention was investigated thoroughly in a pilot study [5]. As a result, we do not find it necessary to establish a data monitoring committee in this trial, and no auditing procedures has been specified.

Through a new digital medical record system which was implemented in the clinic in 2022, the research group is automatically notified of possible adverse incidents, which are logged as part of the study. Should unexpected or adverse incidents occur or be otherwise reported, the steering group will be informed as soon as the incident is known and will decide on further handling. Participants are all patients at CMHC and receive standard treatment and follow-up according to standard clinical procedures.

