Both a published paper from the European Refinement group and statistics from World Health Organization demonstrate that Norway is in recent years one of the countries with the highest number of public mental health workers per inhabitant [37, 38]; still, waiting lists are increasing, and a shortage of resources is reported. Nevertheless, since both over- and undertreatment of mental illness can be harmful [39, 40], it might be good to evaluate the organisation of services. It is important to ensure that referred patients who are likely to benefit from measures other than medical and/or psychological assessment and treatment are offered such options instead of, before, or in parallel with specialised mental health care. To this end, better integration and coordination of health and other care services have been called for [41]. Interaction with other contributors in health and social services—such as primary health care, community services, or social security services—may be needed to find the right follow-up measures for many of those being referred. This will benefit not only the individual but also the mental health services, by ensuring that there is sufficient capacity for patients with severe mental disorders who need specialised mental health care treatment. From a societal perspective, the health care offered should contribute to reducing social security benefits by increasing the level of functioning.

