To take on more efficient ways to handle and triage elective referrals to an outpatient clinic, an Early assessment Team (EaT) was established at St. Olav’s University Hospital, Nidelv CMHC, Tiller, in 2017. The purpose was to help patients with an unclear referral receive adapted health care, in line with the national CMHC guidelines and the Health Care Interaction reform [47, 48]. The working method was developed within the frame of the Crisis Resolution Team (CRT), present in the unit since 2008, and drew on experiences from general outpatient clinics over time [49]. The work method in EaT differs from ordinary assessment and follow-up in a general outpatient clinic: it offers a team-based clarification within a few weeks after referral, patients’ problems are understood from a broad perspective (i.e. a biopsychosocial and contextual approach), and the team is organised in a way which supports greater flexibility and accessibility then what is usually possible in a general out-patient clinic. The focus is on immediate collaboration with the community, GP, workplace, etc., and the approach entails identifying patients’ present symptoms and functional strife, rather than establishing an exact diagnosis.

A pilot study evaluating the EaT methodology over its first 2 years indicated a potentially positive effect [5]. More than a thousand patients were referred to EaT who were regarded as in need of service based on written referral. After EaT assessment, two-thirds of these patients were considered to be not in need of further follow-up in a general psychiatric outpatient clinic; this was clarified over the course of 1–3 meetings in 90% of the cases. Less than 20% were re-referred within 6 months, and patients expressed satisfaction with the treatment. However, the effect of the model has not been tested with scientific methods which support generalisation.

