## Discussion

This protocol describes a randomised controlled study which aims to determine the effect of a novel way of assessing newly referred patients to outpatient specialised mental health care.

A better organisation of the system to assess who does and who does not need further assistance from mental health care may likely lead to greater capacity for those who need the specialist service. If the model gives rise to a secure, sustainable organisation of services, it should be broadly implemented; similarly, if the model reveals important weaknesses, these should be shown and addressed, or else the model may need to be adapted or ignored.

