## Trial status

This publication is based on protocol version 1 (ClinicalTrials.gov publication date, 21 October 2021). Recruitment for the trial began on 25 October 2021 and is expected to be completed by 2024.

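### The no-harm rationale leaves out undertreatment after early closure, the only specified incident capture starts after recruitment, and no by-arm comparison of logged incidents is stated

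*Protocol article*

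**What the plan says.** **Rationale.** Data monitoring and safety states: "No harmful consequences of participation in this study are anticipated; therefore, no stopping guidelines have been developed". Interim looks at the data are ruled out on the same ground. The reasons given are that the right to health care is unaffected, nothing invasive is done, and a pilot examined the intervention thoroughly. From these the section concludes: "we do not find it necessary to establish a data monitoring committee in this trial, and no auditing procedures has been specified". It ends by saying that all participants are patients of the centre and get the usual treatment and follow-up.

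**Incident capture.** The same section relies on "a new digital medical record system which was implemented in the clinic in 2022, the research group is automatically notified". Events flagged this way are kept in a study log. Incidents that come to light in some other way also go to the steering group, but that route is not described. Under Trial status: "Recruitment for the trial began on 25 October 2021".

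**Passages on the mechanism of harm.** The Background argues for evaluating how services are organised "since both over- and undertreatment of mental illness can be harmful". Of the pilot it reports that "two-thirds of these patients were considered to be not in need of further follow-up in a general psychiatric outpatient clinic", settled within 1–3 meetings in 90% of cases. It adds that the model's effect has not yet been tested by methods that allow generalisation. Under Interventions, EaT ends a patient's contact with the centre when other measures are expected to suffice.

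**Use of the result.** The Discussion says: "If the model gives rise to a secure, sustainable organisation of services, it should be broadly implemented".

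**The concern.** EaT is a triage intervention, and one of its intended outputs is a decision that a referred patient needs no further care at the centre. If that decision is wrong, the harm is an untreated or undertreated patient. That a procedure is non-invasive says nothing about this risk. An uncontrolled pilot, reported here with re-referral and satisfaction figures only, says little.

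Two features of the incident log then matter. First, it was not automatic for the earliest enrolments. Second, it is fed by the clinic's own record. A patient in continuing TAU appears in that record often. An EaT patient whose contact has ended may appear rarely. Fewer logged incidents under EaT could then reflect less observation rather than less harm, which is the direction that would make EaT look safer.

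At stake is whether a later statement that the model is safe enough to spread could be traced to a stated comparison with equal ascertainment in the two arms.

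**Working it through.** **The plan's own figures.** The safety section contains none. The sample size supplies the denominators used below and reproduces: for a difference of 3, SD 10, two-sided 0.05 (sidedness assumed) and 80% power, the t-test needs 175.4, so 176 per arm; 176/0.6 = 293.3, so 294 per arm and 588 in total.

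**Step 1: rationale against the rest of the document.**

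| Data monitoring and safety | Elsewhere in the article |
|---|---|
| No harm anticipated | Undertreatment can be harmful (Background) |
| Pilot was thorough | Effect not tested by generalisable methods (Background) |
| All participants receive usual treatment and follow-up | EaT may end contact with the centre (Interventions) |

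The third row must be reconciled. The first two show that the rationale leaves out the relevant mechanism. If the pilot share carried over, 2/3 × 294 = 196 EaT patients would not continue in the general clinic. That is an inference from the pilot; the protocol states no such figure for the trial.

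**Step 2: length of the capture gap.** The go-live month in 2022 is not given, so the range runs from the first to the last day of that year.
- 25 October 2021 to 1 January 2022: 68 days.
- 25 October 2021 to 31 December 2022: 432 days.

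**Step 3: participants enrolled before go-live.** Statistical analyses gives 294 included by 20 September 2023, which is 695 days after the start. Assuming constant accrual, the rate is 294/695 = 0.423 per day.
- Earliest go-live: 0.423 × 68 = 28.8, about 29 (29/588 = 5%).
- Latest go-live: 0.423 × 432 = 182.7, about 183 (183/588 = 31%).

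**Step 4: follow-up time affected.** These participants were covered after go-live, so the share of 12-month follow-up without automatic capture is smaller.
- Earliest: 0.423 × 68²/2 = 978 days, about 2.7 person-years; 2.7/588 = 0.5%.
- Latest: 0.423 × (365²/2 + 67 × 365) = about 38,520 days, about 105 person-years; 105/588 = 18%.

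**Step 5: what a by-arm comparison could show.** The document gives no event rates, so these are assumed. With 294 per arm and two-sided 0.05, power to detect a doubling is:

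| TAU vs EaT | Power |
|---|---|
| 1% vs 2% | 17% |
| 2% vs 4% | 30% |
| 5% vs 10% | 63% |
| 10% vs 20% | 93% |

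For 2% vs 4%, the 95% half-width is 1.96 × √[(0.02 × 0.98 + 0.04 × 0.96)/294] = 2.8 percentage points, so a true difference of 2 points would come with an interval of about −0.8 to 4.8. With no events in 294, the one-sided 95% upper limit is 1 − 0.05^(1/294) = 1.0%. Estimates with intervals are therefore informative; a significance test for rare events would not be.

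**The case against.** A reader might infer that no harm outcome is compared between arms. The document does not support that. CORE-OM contains six items on risk to self or others, Table 1 schedules it at baseline and 12 months, and Statistical analyses compares the secondary outcomes between the randomised groups. WSAS and the well-being scales can show worsening. Use of health services is among the outcomes to be compared, and records are screened for mental and somatic specialist contacts. Itemised harm tables may also stand in the full protocol or SAP, which are not shown, so their absence from an article is not in itself a fault. What remains is that the article states no separate analysis of the risk items and no by-arm comparison of logged incidents. Self-reports face an assumed 40% drop-out, and a lower count of contacts can mean either efficiency or unmet need.

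A reader might also take the date gap as a source of bias. Randomisation is concurrent, so the gap falls on both arms; it lowers capture without an evident reason to favour either. The second reporting route and the 12-month record review also reach the early participants. The possible bias is the separate one, unequal observation once contact has ended, and that is plausible rather than shown.

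The clinical safeguards deserve weight. Patients obviously needing emergency or long-term specialised care are excluded, EaT can offer short-term follow-up and transfer to the general clinic, and fewer than 20% of pilot patients were re-referred within 6 months. These reduce the risk of undertreatment but do not remove it. Doing without a monitoring committee and interim analyses in a service-organisation trial is an explained choice and is not contested here.

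**Conclusion.** The point holds in a limited form:

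- The no-harm rationale does not address undertreatment after early closure, and its closing statement on usual follow-up needs reconciling with the description of EaT.
- Automatic incident capture misses the first 68 to 432 days of recruitment. About 29 to 183 participants (5% to 31% of 588) enrolled before it, and about 0.5% to 18% of 12-month person-time is affected. Both ranges assume constant accrual and reflect the unstated go-live month.
- No by-arm comparison of logged incidents is stated, and the log may under-record events in EaT patients whose contact has ended.

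It would go too far to conclude that the trial cannot support a finding that the model is secure. In the Discussion that word is a condition for implementation, followed by an undertaking to show and address weaknesses; it is not a planned conclusion. The document simply does not state which analysis would show that the condition is met. Nor does the protocol say that EaT is expected to end contact for most trial participants; that is read across from the pilot.

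**What to change.** 1. In the 12-month record review already planned for both arms, extract a short predefined harm set: acute psychiatric admission or emergency contact, recorded self-harm or suicide attempt, death, and re-referral.
2. Use a fixed window of 0–12 months from randomisation, applied identically to everyone enrolled since 25 October 2021 and whether or not contact with the centre has ended.
3. Analyse the CORE-OM risk items already collected at T5 separately by arm.
4. Report rates and between-arm differences with 95% CIs as descriptive estimates, and say that rare events cannot be excluded at this sample size.
5. State the go-live date of automatic notification and describe the other reporting route.
6. Correct the rationale in Data monitoring and safety so that it acknowledges undertreatment, and reconcile the statement about usual follow-up with the Interventions section.

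The cost is a few extra fields in an existing review and a look-back for early participants, with no added patient burden. One limit remains: events handled wholly outside specialist services may not appear in hospital records, and the report should say so.
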